### Statistics

#### Sample size calculation

A sample size of 100 participants in the intervention group and 150 in the control group will reach a power of 80% at a two-sided level of significance of 5% to detect a difference in the EORTC QLQ-C30 (scores range from 0 to 100) with a Cohen’s d effect size of 0.4 (mean difference of ten scores and standard deviation (SD) of 25 scores) [11]. Given that the effect size might be smaller due to a lower mean difference or higher SD, and that the severity of cancer can cause higher dropout rates, we aim to include 150 participants in the intervention group and 200 in the control group (so a total sample size of 350 participants).

The sample size calculation based on the t-test was used in spite of the intended analysis with a baseline-adjusted repeated-measures linear mixed model (ANCOVA, three-level random intercept model to account for repeated measures in patients and clustering in centers). It can be shown [22] that a conservative approach for estimating sample sizes has the same power as a t-test with n subjects where p is the variance deflation factor, calculated by the correlation of baseline and follow-up measures. Assuming the worst case of *p* = 0 leads to the sample size based on the t-test.

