#### Statistical analysis plan

All statistical tests are performed using Stata IC15 (StataCorp, 2017, College Station, TX, USA). The primary hypothesis will be tested at a two-sided significance level of α = 0.05. All secondary hypotheses will be tested within an exploratory framework.

Descriptive statistics and the number of participants reflected in the calculation (n) will be presented in each group. For continuous variables, mean with SD for normal distribution and median with interquartile range (IQR) for other distribution variables will be presented. For categorical data, frequencies and percentages will be displayed for each category. Graphic methods such as box plots and line graphs will be used for visualizing the data.

The comparison of EORTC QLQ-C30 (global health status as a primary outcome), physician-patient communication (scores), health competence (scores), participation (scores), and knowledge (scores) over the study period between the groups will be reported as mean and 95% CI, and performed using a linear mixed model (LMM) with three levels over all available time points. Random intercepts for the patient ID and for the study clinics are included in the model to account for the cluster structure of the data. To keep selection bias to a minimum, we will develop a propensity score for adjusting baseline factors. The propensity score will be used with the inverse probability of treatment weighting (IPTW) method because the results from this method are similar to a randomized trial [23, 24].

The number of outpatient visits will be counted and the study time will be calculated over the follow-up time for each patient. The incidence rate of outpatient visits per person-time will be presented, and Poisson regression will be used to compare the incidence rate between groups.

All outcomes will be analyzed using modified intent-to-treat populations including all subjects who receive at least one consultation from an SCN and for whom at least the first follow-up assessment at Visit 1 (at 3 months) is available.

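### IPTW is paired with a three-level random-intercept model: on observations most of the weighting is lost, and on patients the standard error must not rest on four clinics

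*Protocol article*

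**What the plan says.** All of this is in the protocol article, Module 1, under Statistics.

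- The section Statistical analysis plan names the EORTC QLQ-C30 global health status as primary outcome, analysed by a linear mixed model with three levels. It states: "Random intercepts for the patient ID and for the study clinics are included in the model".
- The section Sample size calculation describes the same analysis as baseline-adjusted (ANCOVA) and as a "three-level random intercept model to account for repeated measures in patients and clustering in centers".
- Confounding is handled by weighting: "The propensity score will be used with the inverse probability of treatment weighting (IPTW) method".
- On the test: "The primary hypothesis will be tested at a two-sided significance level of α = 0.05". On software: "All statistical tests are performed using Stata IC15".
- Participant recruitment gives four hospitals, with both groups recruited at the same sites, and follow-up at 90, 180 and 365 days. Group membership follows the insurer.

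The article does not say at which level the weights enter, whether they are stabilised, or which standard error goes with them.

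**The concern.** The Discussion names selection bias as a worry and relies on IPTW against it. IPTW does that job only if a patient with weight w counts w times in the treatment contrast. In a random-intercept model that depends on where the weight is attached.

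- **On observations.** A patient's weight is the same at every visit, so it only rescales that patient's residual variance. The patient remains one cluster with one random intercept, and the weight has little influence on how much that patient counts. A balance table made with the raw weights would still look good, so nothing would warn the analyst.
- **On patients.** The weights act in full, but the standard error becomes the issue. Model-based errors treat the weights as real replication. A sandwich sums over independent units, and in the stated model the only independent units at the top are the clinics, of which there are four.

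At stake is either bias left in the primary estimate or a primary p-value and confidence interval that are too optimistic.

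**Working it through.** **Inputs from the article.** Four clinics; three follow-ups; target 150 and 200 patients; difference 10, SD 25, d = 0.4; two-sided 5%.

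**Assumed, because the article gives no figure.** Intraclass correlation (ICC); one measured confounder with a 0.3 SD effect on the score at every visit, baseline included, and a standardised mean difference (SMD) between groups of 0.83 (0.47 as the weaker case); clinic variance share 0.02.

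**1. The plan's own power figure.** The stated inputs are "A sample size of 100 participants in the intervention group and 150 in the control group" and "mean difference of ten scores and standard deviation (SD) of 25 scores", for 80% power. Noncentrality is 0.4 × √(100 × 150/250) = 3.10, and Φ(3.10 − 1.96) = 0.87. So the power is 87%; 80% would need about 82 and 123. The stated figure is conservative and has no bearing on this point.

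**2. Effective weight when weights sit on observations.** With n visits and constant weight w, a patient's mean has variance τ² + σ²/(nw). With total variance 1, the patient counts as

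f(w) = 1 / [ICC + (1 − ICC)/(nw)].

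For n = 3, w = 5, ICC = 0.6: (0.6 + 0.1333)/(0.6 + 0.0267) = 1.17. An intended 5:1 ratio becomes 1.17:1. At ICC 0.3, 0.4, 0.5 and 0.7 it becomes 1.54, 1.36, 1.25 and 1.11.

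Baseline adjustment lowers the relevant ICC. With equal correlation ρ between all visits, it becomes (ρ − ρ²)/(1 − ρ²) = ρ/(1 + ρ), that is 0.29, 0.375 and 0.43 for ρ = 0.4, 0.6 and 0.75. The weights then survive a little better, but not well: at 0.375 the ratio is (0.375 + 0.2083)/(0.375 + 0.0417) = 1.40.

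**3. Bias in the fitted three-level model.** 600 simulated trials per setting, 350 patients, true effect 0, estimated propensity score, stabilised weights, SMD 0.83. Bias in points is SD units × 25.

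| ρ | Baseline-adjusted | Unweighted | Observation weights | Share left | Patient weights |
|---|---|---|---|---|---|
| 0.4 | no | 6.1 | 4.4 | 72% | 0.0 |
| 0.6 | no | 6.1 | 5.2 | 84% | 0.0 |
| 0.75 | no | 6.1 | 5.6 | 91% | 0.0 |
| 0.4 | yes | 3.7 | 2.2 | 61% | −0.1 |
| 0.6 | yes | 2.4 | 1.7 | 69% | −0.1 |
| 0.75 | yes | 1.5 | 1.1 | 72% | −0.1 |

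For the weaker confounder, from the formula: 0.471 × 0.3 × 25 = 3.5 points unadjusted. After baseline adjustment at ρ = 0.75 this is 3.5 × (1 − 0.75) = 0.9. The share left at ICC 0.4 is 0.69 (stabilised) or 0.81 (unstabilised), so about 0.6 to 0.7 points stay.

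**4. Type I error with patient weights** (test centred on the mean estimate, ranges over the three values of ρ).

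| Standard error | Unadjusted | Baseline-adjusted |
|---|---|---|
| Model-based | 6-8% | 10-11% |
| Four-clinic sandwich, 1.96 | 10-11% | 14-16% |
| Four-clinic sandwich, t with 3 df | 3-4% | 4-5% |
| Patient-level sandwich, 1.96 | 3-4% | 4-6% |

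With 600 trials, the Monte Carlo standard error at 5% is √(0.05 × 0.95/600) = 0.9 percentage points, so the lowest model-based figure is hardly distinguishable from 5%. The four-clinic standard error itself varies with a coefficient of variation of about 0.44.

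**5. Power cost of t with 3 df.** The critical value is 3.18. For d = 0.4, power is about 56% at 100/150 and 70% at 150/200, against 87% and 96% for the normal test, before any loss from weighting.

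**The case against.** The strongest reply is that weight level and variance estimator are details that an article leaves to the full analysis plan, which is not shown, and that the fault lies in implementations the article never names. Their absence is indeed no finding in itself. What stands is narrower: the article does fix the model structure, twice, with the clinic as top random level, and adds IPTW to it. A plan that follows this text is led to one of the fits above unless it departs from the stated structure or adds a specific choice of weights and standard error.

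Three stronger readings are tempting, and the documents support none of them.

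- A reader might infer that IPTW cannot work in a random-intercept model. It can: patient-level weights with a patient-level sandwich removed the bias and held the level.
- A reader might infer that IPTW is the only protection against bias. The sample size section adjusts for baseline, which in the simulation cut the unweighted bias from 6.1 to between 1.5 and 3.7 points.
- A reader might infer that the primary standard error necessarily rests on four clinics. The article states no such variance, and because both groups are recruited within each clinic, the contrast itself does not depend on having only four.

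It is also fair that ICC, confounder strength and clinic variance are assumed. More than half of the confounding stays under observation weights for any ICC of about 0.25 or more; below that, with stabilised weights, it is about half.

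**Conclusion.** The point holds as a conditional one. With observation-level weights, about 60-73% of the measured confounding that remains after baseline adjustment stays in the primary estimate, roughly 0.7 to 2.2 points on a 100-point scale, and about 70-90% stays without that adjustment. With patient-level weights the bias is removed, but model-based errors gave 6-11% type I error and a four-clinic sandwich 10-16% against the normal reference. Using t with 3 df repairs the level but brings power down to about 56-70%.

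The ranges rest on correlations of 0.4 to 0.75, three follow-ups, stabilised weights and the assumed confounder. The mechanism, a constant weight absorbed by the patient intercept, does not depend on these values; its size does. Because the comparison is non-randomised and this is the confirmatory test, the choice should be settled before the analysis.

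**What to change.** State that the weights act at patient level and make the patient the highest level, with clinic as fixed indicators and baseline global health status as covariate. Either of two estimators will do:

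1. A weighted marginal model of the follow-up scores on group, visit, baseline score and clinic, by weighted least squares or GEE with independence working correlation.
2. A two-level mixed model with patient-level weights.

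In both, cluster the standard errors on the patient, or bootstrap patients within clinic and group and re-estimate the propensity score in each sample. Use the same estimator for the secondary scores.

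The simulation covered patient-level weights with a patient-level sandwich in the three-level fit. The fixed-clinic and bootstrap variants were not simulated there, so a short check on simulated data before database lock is sensible.

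The cost is wording in the analysis plan and a few lines of code; no new data are needed. The downside is a small loss of efficiency against a correctly specified mixed model.

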### Study objectives

Primary objective:

To compare quality of life over study period between the intervention group (patients who had met an SCN) and the control group (Module 1).

Secondary objective:
To compare the health literacy, participation, and physician-patient communication in the intervention and control groups (Module 1)To explore the associations between quality of life and health literacy, participation, and physician-patient communication (Module 1)To compare the incidence rate of outpatient visits in both groups (Modules 1 and 2)To compare the healthcare costs in both groups (Module 2)To assess the SCN’s practical experiences (Module 3)

### Inclusion and exclusion criteria for participation in the evaluation survey in modules 1 and 2

Inclusion criteria:
Aged ≥18 yearsAt least a combination of one type of cancer and one operation and procedure, as defined by the ICD and OPS codes listed in Additional file 1

Exclusion criteria:
Advanced dementiaAcute addictions

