#### Statistical analysis plan

Paired t-test or Wilcoxon signed rank test will be performed to compare the costs of treatment per month. The generalized estimating equation (GEE) for Poisson regression will be applied to compare the incidence rate of hospitalization and outpatient visits between intervention and matched controls. Kaplan-Meier curve and Cox regression analysis will be performed to compare time-to-death between the groups.

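### The Module 1 Poisson comparison of outpatient visit rates makes no stated allowance for overdispersion, so its confidence intervals would be too narrow if model-based standard errors are used

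*Protocol article*

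**What the plan says.** Comparing outpatient visit rates between the groups is a secondary objective for Modules 1 and 2 (protocol article, Study objectives). For Module 1, the Statistical analysis plan under Statistics gives the data structure: "The number of outpatient visits will be counted and the study time will be calculated over the follow-up time for each patient". Rates are presented per unit of person-time, and "Poisson regression will be used to compare the incidence rate between groups". Nothing further is said about this model.

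Three other statements bear on the point:

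- Clustering is addressed in the same section for the linear mixed model: "Random intercepts for the patient ID and for the study clinics are included in the model to account for the cluster structure of the data".
- The propensity score is introduced at the end of the paragraph on the linear mixed model, in general terms: "To keep selection bias to a minimum, we will develop a propensity score for adjusting baseline factors". It is to be used by inverse probability of treatment weighting (IPTW).
- On inferential status, "The primary hypothesis will be tested at a two-sided significance level of α = 0.05", whereas "All secondary hypotheses will be tested within an exploratory framework".

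**The concern.** A Poisson model assumes that, given covariates and exposure time, the variance of a patient's count equals its mean. If patients in the same group have different underlying visit rates, the variance exceeds the mean and the model-based standard error of the rate ratio is too small.

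The article describes a population in which such differences are to be expected. Eligibility covers any listed pairing of a cancer diagnosis with a procedure. Patients are accompanied for a year whether they are in hospital, outpatients or off treatment. They come from four hospitals in three cities, and the utilization item spans several kinds of therapy and physician. Person-time corrects for unequal follow-up, but not for unequal rates.

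At stake is the credibility of one named secondary result. An interval that is too narrow could make chance variation in visits look like an effect of the programme on utilization.

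**Working it through.** **Inputs from the article.** One count per patient with that patient's person-time; Poisson regression; planned groups of 150 and 200 (Sample size calculation). The two-sided 5% level is fixed for the primary hypothesis only and is used here as a nominal level. The article gives no visit rate, variance, rate ratio or power for this outcome, so there is no figure to reproduce.

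**Assumption.** Var(count) = φ × mean, with φ not known. The range shown starts at φ = 1, where the Poisson model is correct.

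**Step 1, formula.** The model-based standard error is 1/√φ of the true one. The actual type I error of a nominal 5% test is therefore 2 × [1 − Φ(1.96/√φ)], and a correct interval is √φ times as wide. For φ = 2: 1.96/1.414 = 1.386, and 2 × [1 − Φ(1.386)] = 0.166.

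| φ (assumed) | model SE / true SE | type I error | actual coverage of a 95% interval | width factor needed |
|---|---|---|---|---|
| 1 | 1.00 | 5.0% | 95.0% | 1.00 |
| 1.5 | 0.82 | 11.0% | 89.0% | 1.22 |
| 2 | 0.71 | 16.6% | 83.4% | 1.41 |
| 3 | 0.58 | 25.8% | 74.2% | 1.73 |
| 5 | 0.45 | 38.1% | 61.9% | 2.24 |

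**Step 2, what spread between patients gives such values of φ.** If patients' rates follow a gamma distribution with squared coefficient of variation k, then φ = 1 + k × mean count. With k = 0.1 (coefficient of variation √0.1 = 0.32), an assumed mean of 5, 12 or 20 visits gives φ = 1.5, 2.2 or 3.0. A modest spread is enough to reach the middle of the table.

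**Step 3, simulation.** Gamma-Poisson counts with no true difference, 150 against 200 patients, equal follow-up, no weighting, 4,000 runs per setting:

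| mean visits | k | φ | type I error, model-based SE | type I error, robust SE |
|---|---|---|---|---|
| 5 | 0.1 | 1.5 | 11.5% | 5.4% |
| 12 | 0.1 | 2.2 | 19.0% | 5.4% |
| 20 | 0.1 | 3.0 | 25.9% | 4.9% |
| 12 | 0.25 | 4.0 | 32.8% | 5.5% |

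The simulation agrees with the formula. Over all settings run (φ from 1 to 21), the robust standard error kept the error between 4.6% and 5.6%. Simulation error at 5% is about ±0.7 points (1.96 × √(0.05 × 0.95/4000)). At φ = 1 both methods were close to 5%, so the robust version costs practically nothing when the Poisson model holds.

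**The case against.** The strongest reply is that the sentence names a regression model and not a variance estimator. Poisson regression with robust standard errors is compatible with it, and a journal article may leave that detail to the full analysis plan. This stands to the extent that the sentence is incomplete rather than wrong, so the understatement is conditional. It does not dispose of the point. The article fixes a specific method for this outcome, and with default standard errors that method would be poorly calibrated for counts of this kind.

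A second reply is that the outcome is exploratory. That excuses the absence of multiplicity control and limits the importance of the point, but it does not make a standard error valid.

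Two stronger readings are tempting, and the article does not support them:

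- A reader might infer from the order of paragraphs that IPTW is confined to the linear mixed model, and that the visit rate ratio is therefore unadjusted and confounded. The propensity score sentences name no outcome or model, and the Discussion applies the score to the analysis in general when it deals with the non-randomized Module 1 design. The text neither limits the weighting to the linear mixed model nor expressly extends it to the Poisson model. If weights are used, a robust variance is normally needed with them, and that would also deal with overdispersion.
- A reader might see an inconsistency with Module 2, where "The generalized estimating equation (GEE) for Poisson regression will be applied to compare the incidence rate of hospitalization and outpatient visits". Module 2 has matched controls, a different control group and a different, unlinked data source. GEE follows from the matching. Module 1 has unmatched groups and one count per patient.

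**Conclusion.** The point holds in a limited, conditional form. As written, the Module 1 count model contains nothing to absorb extra-Poisson variation. If counts are overdispersed, which is likely here, and if model-based standard errors are used, which the article neither states nor excludes, the intervals will be too narrow. The test size then runs from about 11% at an assumed φ of 1.5 to about 38% at 5, with no inflation at φ = 1. These figures illustrate the mechanism under assumed dispersion; they do not estimate it for this trial.

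The matter is minor. It concerns one exploratory secondary comparison and leaves the primary quality-of-life analysis untouched. It does not show that the rate ratio is confounded, or that the two modules contradict each other.

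**What to change.** In the Module 1 Statistical analysis plan, specify the visit comparison as Poisson regression with robust (sandwich) standard errors, or as negative binomial regression. In either case, use log follow-up time as offset, which the person-time wording already implies. State in the same place that the IPTW weights and a clinic term apply to this model as they do to the linear mixed model. With weights in use, the robust variance is the simplest choice because it serves both purposes. Make the change before the outcome data are analysed.

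The cost is a sentence or two of text and a standard software option. Intervals widen by about √φ where counts are overdispersed and hardly at all where they are not.

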#### Dropouts and missing data

Reasons for dropouts will be documented and reported. If patients are alive and missings are assumed to be missing at random (MAR), we will use multiple imputation methods based on ten imputed data sets [25] with multiple imputation by chained equations (MICE).

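### The analysis population is defined by an SCN consultation and an available 3-month assessment: as written no control qualifies, and on the sensible reading patients are still selected on post-baseline events

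*Protocol article*

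**What the plan says.** The last paragraph of the Module 1 statistical analysis plan sets one population rule. It covers every outcome: "All outcomes will be analyzed using modified intent-to-treat populations including all subjects who receive at least one consultation from an SCN". It has two conditions joined by a conjunction:

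- **Consultation:** at least one, as just quoted. No arm is named.
- **t1 available:** "for whom at least the first follow-up assessment at Visit 1 (at 3 months) is available".

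Four other places bear on it:

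- Study objectives gives the primary objective as "To compare quality of life over study period between the intervention group (patients who had met an SCN) and the control group (Module 1".
- Participant recruitment assigns the monthly SCN consultations to the intervention group. Controls are insured elsewhere and are recruited by Study Nurses. Assessments are at t0 and at 90 (t1), 180 (t2) and 365 (t3) days.
- The primary model is a "linear mixed model (LMM) with three levels over all available time points", with a propensity score for baseline factors applied through IPTW.
- Dropouts and missing data says: "If patients are alive and missings are assumed to be missing at random (MAR), we will use multiple imputation methods", with ten data sets by MICE.

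**The concern.** A population rule decides who enters the primary test. This one cannot be applied as worded, because nothing in the article gives a control an SCN consultation. Someone will have to repair it at analysis, and the repair should not be left to a choice made with the data in view.

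The obvious repair does not remove the whole problem. Receiving a consultation and having a t1 assessment both happen after recruitment. In a severely ill cancer population, missing the 90-day questionnaire is plausibly related to quality of life. The study is not randomised, and its stated protection against selection is weighting on baseline factors. Those weights model which group a patient is in. They do not model whether the patient later met a nurse or completed t1.

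**Working it through.** **Step 1. Who is in the population?** The article gives no figure on this point to reproduce, so the rule is applied to each type of patient.

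| Patient | Rule as written | Consultation limited to intervention arm | Rule proposed under fix |
|---|---|---|---|
| Intervention, consultation, t1 | in | in | in |
| Intervention, no consultation, t1 | out | **out** | in |
| Control, t1 | **out** | in | in |
| Either arm, no t1, answers t2 or t3 | out | **out** | in |
| Either arm, alive, t0 only | out | **out** | in, by imputation |
| Either arm, died before t1 | out | out | reported by group; no follow-up score |

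As written, 0 of the 200 planned controls qualify and no between-group contrast can be estimated. With the consultation limited to the intervention arm, all 200 pass that condition and three rows remain at issue. The second row affects one arm only. The fourth and fifth affect both arms.

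**Step 2. Do the planned methods bring these patients back?** The mixed model uses the available time points of patients in the population, and multiple imputation fills gaps for those patients. A living patient without t1 is removed before either method applies, even with t2 and t3 in hand.

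**Step 3. How large could the effect be?** The article states no loss rate. From Sample size calculation: SD 25 and a planned difference of 10 points. Assumptions: no true effect; in each arm the patients with the worst latent status are lost; that status has correlation ρ with quality of life; no baseline adjustment. If a share p is lost, the mean of those retained rises by

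25 × ρ × k(p), with k(p) = φ(z_p)/(1 − p).

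- k(0.05) = 0.1031/0.95 = 0.1086
- k(0.10) = 0.1755/0.90 = 0.1950
- k(0.15) = 0.2332/0.85 = 0.2743
- k(0.20) = 0.2800/0.80 = 0.3500
- k(0.25) = 0.3178/0.75 = 0.4237
- k(0.333) = 0.3635/0.667 = 0.5449

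The spurious difference is 25 × ρ × [k(p₁) − k(p₂)], in favour of the arm with the larger loss p₁:

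| Loss, p₁ vs p₂ | 25 × [k(p₁) − k(p₂)] | ρ = 0.3 | ρ = 0.5 | ρ = 0.7 |
|---|---|---|---|---|
| 15% vs 5% | 4.14 | 1.24 | 2.07 | 2.90 |
| 20% vs 10% | 3.87 | 1.16 | 1.94 | 2.71 |
| 33.3% vs 25% | 3.03 | 0.91 | 1.52 | 2.12 |
| 25% vs 25% | 0 | 0 | 0 | 0 |

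The third row uses the largest losses that the enrolment targets allow: 1 − 100/150 = 33.3% in the intervention group and 1 − 150/200 = 25% in controls. These are margins, not forecasts, since the article enlarges the sample partly to allow for a smaller effect. With 100 and 150 analysed, the standard error is 25 × √(1/100 + 1/150) = 3.23. A shift of 0.91 to 1.52 points then raises the nominal 5% two-sided error of an unadjusted test to about 5.9% to 7.6%.

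If controls have the larger loss, the same figures apply with the sign reversed.

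**The case against.** **The missing controls are a slip of the pen.** The article plans comparisons between groups, reports numbers in each group and writes of populations in the plural. No analyst would run a comparison without controls. This stands: a reader might infer that the study has no analysable control group, and the rest of the article does not support that. What is missing is a few words limiting the criterion to one arm.

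**The t1 criterion is the same for both arms.** A reader might infer that early deaths and withdrawals are removed from the intervention arm alone. They are not. An intervention patient who dies before a first consultation has no t1, and a control who dies in that period has none either. The one-sided part is confined to intervention patients with t1 but no consultation. SCNs recruit the intervention group themselves, so this subset may be small. The article gives no count.

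**Direction and size are assumed.** A reader might infer a bias towards OSCAR. That needs greater loss of sicker patients in the intervention arm, and no loss rate by arm is given. Controls, who have no monthly contact, might lose more. The illustration also ignores the planned baseline adjustment, which would absorb the part of the loss that baseline explains. This stands too, and the figures in the working are illustrations only.

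**The model wording is not a contradiction.** Using all available time points can mean all those within the defined population. This is fair: the t1 rule wastes t2 and t3 data without contradicting the model statement outright.

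**No rule yields follow-up scores for patients who die before t1.** True; the change recovers living patients and makes the deaths visible. None of these replies gives a reason for requiring t1 in particular, or makes baseline weights correct for later selection.

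**Conclusion.** The population rule is wrong as written. It excludes every control, contrary to the primary objective, most likely through a drafting error. Limiting the consultation criterion to the intervention arm cures that. It leaves a one-sided filter of unknown and possibly small size, together with a t1 filter in both arms that discards usable t2 and t3 data and undercuts the planned imputation. Baseline IPTW corrects neither.

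The documents do not fix the size or direction of any bias. Under the stated assumptions, a gap of 10 percentage points in loss gives roughly 1 to 3 points against a planned difference of 10. The rule itself does not create such a gap: that would take unequal t1 completion, or a sizeable subset of intervention patients with t1 but no consultation. The case for correction rests on an unworkable rule governing the primary test, and not on a demonstrated bias.

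**What to change.** Replace the population paragraph in the Module 1 statistical analysis plan with wording such as:

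> The primary population is all enrolled patients with a t0 questionnaire, analysed in the group in which they were recruited, whether or not a consultation took place and whether or not t1 is available.

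Then:

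- Use all t1 to t3 data from living patients under the stated mixed model and MAR imputation.
- Report deaths and other losses before t1 by group.
- Keep the criterion of at least one consultation, for the intervention arm only, as a labelled sensitivity analysis.
- Reword the primary objective, which now describes the "intervention group (patients who had met an SCN"), so that the group is defined by recruitment.

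This is a change of wording and needs no data beyond the existing schedule. It should be settled before analysis; the Discussion describes the evaluation as ongoing. There are two costs. The effect may be slightly diluted by patients who never met an SCN, and the result relies more on MAR for patients with t0 only.
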